### Recruitment procedures

Non-compliance with the intervention will be taken into account at patient, GP or practice level by over-recruiting. Practices will receive email and phone correspondence inviting their participation. Practice recruitment will be dependent on an expression of interest from at least two of their GPs. Practices will be incentivised through payment for local coordination and set-up. GPs will receive a certificate for the training course (Williamson et al. 2007).

For each recruited GP, ten potential patient participants with pre-booked appointments will be screened by GPs, and if eligible, contacted by post ahead of their appointment. They will receive a cover letter, participant information sheet and example consent form. On their arrival in the practice waiting room, the receptionist will provide the patient with a pre-consultation questionnaire.

Patients who do not wish to participate will indicate this with a tick box on the pre-consultation questionnaire. Practices will keep an anonymised log of patients who declined to participate. A tick box on the post-consultation questionnaire will enable patients to opt out of process evaluation interviews and/or from having their case notes reviewed.

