### The intervention

The overarching project ‘VOLITION’ follows the Intervention Mapping framework ([3]) as a means of systematically applying existing literature and relevant theory to each step of intervention development and evaluation. Social and behavioural science theory was used to describe factors affecting older patients’ involvement in decision-making about their healthcare, as well as methods for improvement. Evidence from a systematic review [8], from patient, public and expert opinion and from a focus group study with older patients with multimorbidity and with GPs, enabled the refinement of logic models underpinning this work. The Intervention Mapping process will be published separately.

There are two core intervention components (see Table 2 and Fig. 2 for detail):
A patient tool to facilitate patients to convey their preferences for involvement to the GPA workshop for GPs to train them in shared decision-making orientated communication skills, delivered in the context of the challenges currently facing GPs when consulting with this patient group

**Table 2 Tab2:** The VOLITION intervention applications

Patient support tool^a^	GP workshop
**Central image**	**Delivery and facilitation by a GP**
Illustrates the spectrum of patient preferences for involvement and poses the question “where do you see yourself?”	For the purposes of role-modelling as a means of knowledge transfer
**Phrases to use during the consultation**	**Information provision**
Aimed at facilitating patients to ask for or decline participation in decision-making, accompany the central image.	GP-facilitator provides information regarding the elements of a shared decision-making approach to the consultation, in the context of older patients with multimorbidity.
Phrases are matched to the spectrum of patient preferences for involvement.	GP-facilitator delivers new messages about the potential benefits of shared decision-making. GP-facilitator uses a set of one or more meaningful premises and a conclusion to deliver these messages.

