	**Patient dialogue during index consultation**
	Patient provides a nudge to the GP in the form of a phrase from the patient support tool, informing the GP of their preferences for involvement in decision making about their care.
	Acts as a cue to the GP to adapt their communication skills accordingly.

^a^The support tool will also be displayed as a poster in the waiting room to prompt recall, as well as being available in leaflet form.

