**Fig. 2 Fig2:**
[figure not shown]
The VOLITION intervention

The patient tool will be mailed to eligible patients ahead of their index consultation. GPs will attend the training workshop no earlier than two weeks in advance of the index consultations with participating patients. Patients in the usual care group will receive standard care.

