#### Evaluation of data collection

Table 3 outlines the feasibility measures to be assessed regarding the collection of outcome data.

**Table 3 Tab3:** Evaluation of data collection procedures

Type of data collection (patient-, GP- or researcher-facing)	Components to be reviewed	Methods of analysis	Potential resultant amendments ahead of a definitive, larger trial
Patient-facing (questionnaires)		All patient-facing data collection forms have been reviewed for their suitability by Patient and Public Involvement (PPI) group	PPI members advised on the wording and format of questionnaires. PPI will provide a lay perspective on interpretation of feasibility findings.
	The feasibility of distribution and collection of patient questionnaires by receptionists.	Researcher’s field notes and follow-up correspondence with practices. Process evaluation interviews with patients.	Consideration of distribution by another means e.g. in the post (or email) prior to consultation.
	The appropriateness of collecting demographic data by patient self-report on pre-consultation questionnaires, as opposed to through the medical record.	Review of completeness of relevant items on patient questionnaires. Process evaluation interviews to discuss potential reasons for missing data. Correspondence with practices regarding practicalities of accessing patient demographic data with consent.	Consideration of accessing patient baseline data through practice records.
	Whether patient participants require assistance, encouragement or supervision to complete either of the questionnaires.	Researcher’s field notes and process evaluation interviews.	The provision of assistance to patients when completing questionnaires, e.g. providing staff to assist them or allowing more time pre- or post-consultation to allow the patient to seek help from a third party.
	Issues regarding time taken for questionnaire completion, any difficulties with comprehension of questionnaire items, numbers of questionnaires returned and reasons for missing data	Relevant quantitative data will be reported descriptively. Issues will be explored qualitatively with patients during process evaluation.	Time taken for completion may inform decisions surrounding when and how to distribute questionnaires. Issues regarding comprehension of specific items may lead to rewording with the assistance of the PPI group.

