**Baseline**					
Practice characteristics (list size, location, deprivation)	Prior to randomisation	Practice and Association of Public Health Observatories website	6 practices	Categorical, nominal/ordinal.	Frequencies, to report data descriptively. Logistic hierarchical modelling to estimate between group differences^a^ (random effect on cluster, adjustment for practice location).
Patient age, gender, ethnicity, self-reported health status	Prior to index consultation	Pre-consultation postal questionnaire	180 patients	Categorical, nominal/ordinal.	Frequencies, to report data descriptively. Logistic hierarchical modelling to estimate between group differences (random effect on cluster, adjustment for practice location).
Patient deprivation data from patient postcodes	Following return of patient pre-consultation questionnaires and consent forms	Practice records mapped to the Index of Multiple Deprivation	180 patients	Continuous (IMD scale)	Mean and standard deviation, to report data descriptively. Linear hierarchical modelling to estimate between group differences^a^ (random effect on cluster, adjustment for practice location).
GP age, gender, ethnicity, time since qualification	Prior to index consultation	GP practices and General Medical Council GP registry	18 GPs	Categorical, nominal/ordinal	Frequencies, to report data descriptively. Logistic hierarchical modelling to estimate between group differences^a^ (random effect on cluster, adjustment for practice location).
Patients’ preferences for involvement in decision-making.	Prior to index consultation	Patient pre-consultation postal questionnaire	180 patients (90 per arm)	Ordinal (6 point Likert scale).	Frequencies, to report data descriptively. Logistic hierarchical modelling to estimate between group differences^a^ (random effect on cluster, adjustment for practice location).

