#### Preliminary evaluation of participant responses to the intervention

The intended sample size is sufficient to estimate standard deviations in our intended primary outcome, ‘ratings of shared decision-making during the consultation from an observer perspective’, for the intervention and control group. This outcome data will be obtained from OPTION(5) ratings of video-recorded consultations. No formal power calculations will be carried out and hypothesis testing will not be appropriate [47].

The observer OPTION(5) scores (Elwyn 2014) and the patient and GP ratings of shared decision-making, based on collaboRATE (Elwyn 2014), will be analysed using hierarchical linear modelling with a random effect on cluster. Patient and GP collaboRATE scores will be compared using logistic regression; modelling patient scores as the outcome and GP scores as the explanatory variable, providing preliminary data on whether patient and GP perceptions are congruent.

Patients vary in their pre-existing preferences for involvement in decision-making about their healthcare (Butterworth 2013 [50];). A secondary analysis with adjustment for patients’ reported preference for shared decision-making will provide a preliminary indication as to whether patients’ pre-existing preferences influence the effect of the intervention.

The participant population will be ‘all randomised’ and the analysis strategy will be ‘intention to treat’. There are no plans for interim analysis.

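### Preference for involvement is recorded after the intervention arm has been sent a tool about that preference, so it is not a clean baseline variable and adjusting for it can bias the secondary analysis

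*Protocol article*

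**What the plan says.** **Measurement.** Collecting outcome measure data puts the preference item on the pre-consultation patient questionnaire. Recruitment procedures says when patients get it: "On their arrival in the practice waiting room, the receptionist will provide the patient with a pre-consultation questionnaire". The earlier postal contact in that section consists of a letter, an information sheet and a sample consent form; no questionnaire is listed. Table 3 puts under review "The feasibility of distribution and collection of patient questionnaires by receptionists", and gives as a possible change for a later trial "Consideration of distribution by another means e.g. in the post (or email) prior to consultation".

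**Intervention.** Practices are randomised once recruited. Under The intervention: "The patient tool will be mailed to eligible patients ahead of their index consultation". The footnote to Table 2 adds: "The support tool will also be displayed as a poster in the waiting room to prompt recall". Table 2 says of the tool's central image: "Illustrates the spectrum of patient preferences for involvement and poses the question", the question being where the patient sees himself or herself. The tool's messages cover the patient's right to be involved and the benefits of shared decision-making.

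**Analysis.** Table 4 places preference under its Baseline heading, gives the source as "Patient pre-consultation postal questionnaire", and plans a between-arm estimate. Preliminary evaluation of participant responses to the intervention plans "A secondary analysis with adjustment for patients’ reported preference for shared decision-making", treating preference as pre-existing and as a guide to whether it influences the intervention effect.

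**The concern.** A covariate can be adjusted for safely in a randomised comparison when allocation cannot have changed it. Here one arm answers the preference question after being sent material on that very question, in a room where the material is displayed, and the other arm does not. If the answers move as a result, adjustment subtracts part of what the intervention did, or compares patients who are no longer alike across arms. A between-arm difference in preference could then come from the tool as well as from who was recruited.

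The main stake is the definitive trial. This study exists to settle data collection and analysis for it, and the Discussion cites review advice to correct results for reported preference. A mistimed covariate could be carried forward.

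**Working it through.** **1. Order of events in the intervention arm, as the text stands.** Practice recruited; practice randomised; tool mailed to the patient; patient arrives where the poster hangs; receptionist hands over the questionnaire; patient states preference; consultation. In the control arm the two tool steps are absent. Preference is therefore measured after randomisation and after exposure.

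**2. Does the postal label in Table 4 change this?** It contradicts Recruitment procedures and Table 3, where post is only a later alternative. Even a posted questionnaire would follow randomisation of the practice, and nothing in the protocol places it ahead of the tool.

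**3. Which analyses use the variable?** There are two: the Table 4 between-arm comparison of preference and the preference-adjusted secondary analysis. The Table 4 model for OPTION(5) has a random effect for cluster and adjusts for practice location only.

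**4. Size.** There is no figure in the plan to reproduce. It gives no power calculation, effect size, standard deviation or preference-outcome slope, so every input below is an assumption. Let d be the shift in measured preference caused by the tool (in SDs of preference), b the outcome slope per SD of preference, and 0.3 the direct effect, with independent outcome error of SD 1.

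- Without a shared cause: total effect = 0.3 + b × d; adjusted effect = 0.3; bias = -(b × d).
- With an unmeasured shared cause (loading 0.5 on preference, 0.25 on outcome): it adds 0.5 × 0.25 = 0.125 to the fitted slope, so bias = -d × (b + 0.125).

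A linear simulation with 400,000 patients per setting gave the following (differences taken before rounding):

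| Shared cause | b | d | Total effect | Adjusted, preference as measured | Bias | Adjusted, preference before the tool |
|---|---|---|---|---|---|---|
| no | 0.4 | 0 | 0.298 | 0.300 | +0.002 | 0.300 |
| no | 0 | 0.5 | 0.303 | 0.303 | -0.001 | 0.303 |
| no | 0.2 | 0.2 | 0.337 | 0.297 | -0.040 | 0.338 |
| no | 0.2 | 0.5 | 0.398 | 0.299 | -0.100 | 0.398 |
| no | 0.4 | 0.2 | 0.376 | 0.299 | -0.078 | 0.379 |
| no | 0.4 | 0.5 | 0.495 | 0.295 | -0.200 | 0.496 |
| yes | 0.4 | 0 | 0.305 | 0.304 | -0.001 | 0.304 |
| yes | 0 | 0.5 | 0.301 | 0.238 | -0.062 | 0.300 |
| yes | 0.4 | 0.5 | 0.499 | 0.239 | -0.261 | 0.501 |

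The formulas agree: -(0.4 × 0.5) = -0.200; -0.5 × 0.125 = -0.0625; -0.5 × 0.525 = -0.2625. With d = 0 there is no bias beyond simulation error. Adjusting for preference as it stood before the tool leaves the total effect intact.

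**5. If only the written answer moves.** Suppose the underlying preference P is unchanged and the recorded value is M = P + d in the intervention arm. Then outcome = 0.3 × arm + b × P + error = (0.3 - b × d) × arm + b × M + error. The total effect is 0.3, the adjusted effect is 0.3 - b × d, and the bias is again -(b × d).

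**6. On the native scales.** Assumed shifts of 0 to 1.0 point on the 6-point item and slopes of 0 to 4 OPTION(5) points per point give 0 × 0 = 0 up to 1.0 × 4 = 4 OPTION(5) points.

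**The case against.** **The tool may not move preference.** Its stated purpose is to help patients tell the GP what they prefer, and its phrases let them turn involvement down as well as request it. This stands as far as it goes: a shift is plausible from the messages on rights and benefits, but it is not stated. Step 5 shows that a change in the answer alone, with no change in underlying preference, would be enough.

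**The timing is not beyond doubt.** Table 4 says postal in two rows, and the examples of missing data include patients who fill in questionnaires but do not attend. Figure 1, the assessment schedule, was not available for this review. This supports treating delivery as an internal contradiction to settle first. Recruitment procedures and Table 3 still point to the waiting room.

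**The reach is narrow.** One secondary analysis, described as preliminary, is affected, in a study without hypothesis tests and not powered for effect. No progression criterion depends on it. All of this stands.

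A reader might infer more than the protocol supports:
- *That the adjustment does bias the effect.* It does so only if stated preference shifts and preference or a shared cause relates to outcome.
- *That the main OPTION(5) result is compromised.* That model does not contain preference.
- *That a preference difference would be read as selection bias.* No section says so. The protocol ties selection bias to unequal drop-out or recruitment between arms, and its other remark on between-group differences concerns missing outcome data.
- *That a given share of the effect is lost.* This needs a shift, a slope and an effect size, none of which the protocol gives.

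**Conclusion.** The point holds in a limited form. As the text stands, preference is a post-exposure variable in the intervention arm, while Table 4 and the secondary analysis treat it as baseline and pre-existing. The secondary analysis can therefore bias the estimated effect, and the between-arm preference comparison is not a clean baseline comparison. The bias is zero if the tool causes no shift. Under the assumed standardised inputs it ranges from 0 to -0.20 without a shared cause and to about -0.26 with one. Its sign follows the direction of the shift and of the slope, which the protocol does not fix.

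The planned analysis also cannot show whether pre-existing preference influences the effect. Adjusting for a main effect does not test that, and an arm-by-preference interaction would still sort patients by a variable the tool may have changed. The conclusion rests on waiting-room delivery being the operative procedure.

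**What to change.** 1. Reconcile Recruitment procedures, Table 3 and Table 4 on how and when the pre-consultation questionnaire reaches the patient, and state its order relative to the tool. This is an editing change.
2. If it can be done within the consent process, collect the preference item before the tool is received. This costs an extra mailing with a return step before a pre-booked visit, and a consent and ethics amendment. The amendment is not trivial: the GP takes written consent at the start of the consultation, and refusal is recorded on this same questionnaire.
3. Otherwise, move preference out of Baseline in Table 4 and report it by arm as a possible response to the intervention. Either drop the preference-adjusted analysis or present it as conditioning on a post-exposure variable, not as evidence on whether pre-existing preference influences the effect. This is nearly free; the price is the loss of a clean preference-adjusted result.

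Whichever route is taken, the timing should be settled before the adjustment is carried into the definitive trial.

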### Consent

Written consent from GPs will be obtained at the time of practice recruitment. Consent to identify and approach potential patient participants will be obtained from the practice manager. Written consent from patients will be obtained by the GP at the start of the consultation. GPs will be expressly clear that they are not part of the research team when taking consent. Written informed consent will be obtained prior to interviews for process evaluation purposes by the Chief Investigator. Where possible, reasons for participants declining participation will be recorded anonymously by the Chief Investigator or by GPs. Identifiable data will not be accessed without prior patient consent.

### Randomisation and blinding

The study will use a cluster randomised design. Clusters will be defined at practice level, with practices randomised 1:1 to usual care or to the intervention (90 patients per arm) following recruitment. Block randomisation will be stratified by site; two practices in inner city Plymouth, two practices from Exeter and two from rural Devon.

Randomisation will be conducted by an independent statistician who is blinded to the identity of practices. Blinding of the research team to outcome assessment will not be possible due to resource availability. Blinding of participants is unlikely to be achievable as participants in the intervention arm are likely to be aware that they are receiving more than standard ‘usual care’.

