#### Collecting outcome measure data

The General Practice Patient Survey (GPPS) uses five-point Likert scales [10]. A subset of these are appropriate for evaluation of Patient Reported Outcome Measures (PROMs) [13] on the pre-consultation patient questionnaires. These questionnaires will also be used to collect patients’ pre-consultation preferences for involvement in decision-making.

A post-consultation patient questionnaire will be used to collect post-consultation PROMs. Data will include the extent to which patients felt engaged in decision-making [2], their satisfaction with care and patient empowerment [27]. A post-consultation questionnaire for GPs will collect GPs’ ratings of the extent to which they felt they involved the patient in decision-making.

Video-recordings will enable the shared decision-making process to be assessed from an observer perspective using the OPTION(5) scale (Elwyn 2014). Two researchers will independently score each clinical decision made out of 100, with higher scores indicating better shared decision-making.

Case note review by two independent researchers will take place 12 weeks after the index consultation (to ensure time for documentation of the required outcomes). Information collected will include re-attendance within 28 days and referral for investigation or to secondary care.

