### Analysis

#### Recruitment capability, consent and randomisation procedures, sample characteristics

The trial will determine whether it is possible to recruit appropriate study participants to test the intervention, or whether amendments are required ahead of a future trial. The flow of participants will be summarised in a Consort diagram. Numbers of eligible clusters, individual participants identified and randomised, recruitment rates and attrition will be recorded.

The search strategy used to identify potentially eligible patients will be tested on different practice databases with a view to finalising a generic, universal search algorithm. Anonymised data on ineligible patients will provide a profile of those frequently excluded. Consideration will be given to whether adaptations to the trial could be appropriate, to enable these patients to participate in a future study.

Any difficulties with meeting recruitment targets (6 practices; at least 2 GPs per practice; at least 5 patients per GP) will be documented. Field notes and correspondence with practices will enable the issues to be explored. Patients’ reasons for declining will be reviewed in light of recruitment procedures. For example, patients will use the pre-consultation questionnaire to indicate whether they received the information pack in the post. The extent to which over-recruitment is necessary will be reviewed, as will the importance of incentivising participants.

Randomisation procedures will be discussed at team meetings to inform amendments prior to a larger trial. For example, consideration will be given to randomising more practices to the intervention than to usual care, to gather more data regarding intervention implementation if required. Consideration will be given to initiating the study in each of the three sites sequentially (e.g. inner city, then urban, then rural) in order to increase trial management capacity. Consideration will be given to blinding the research team for data analysis in the future trial.

Rates of patient consent, to the use of questionnaire data, to video-recording ([12]; Asan and Montague 2014) and to case note review, will be evaluated. Numbers lost to follow-up will be reviewed; however, it is anticipated that this will be minimal. The study will determine whether there are differential drop-out or recruitment rates between intervention and control groups (indicative of selection bias).

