GP-facing (questionnaires and patient consent forms)	Issues regarding time taken for consenting patients, any difficulties with comprehension of items and reasons for missing data	Relevant quantitative data will be reported descriptively. Issues will be explored qualitatively with GPs during process evaluation.	Amendments to wording of consent form. Re-costing of incentive payments to practices if necessary, for extra consultation time to allow for consent.
	Issues regarding operation of video-camera to record consultation	Rates of incomplete, unusable or missing recordings will be reported. Issues will be explored qualitatively with GPs during process evaluation, through the researcher’s field notes and through correspondence with practices regarding any setup difficulties.	Review of existing technology and equipment provided, consideration of the need for prompts for GPs to initiate videos
	Issues regarding time taken for questionnaire completion, any difficulties with comprehension of questionnaire items, numbers of questionnaires returned and reasons for missing data	Relevant quantitative data will be reported descriptively. Issues will be explored qualitatively with GPs during process evaluation.	Issues regarding comprehension of specific items may lead to rewording. Re-costing of incentive payments to practices if necessary, for extra consultation time to allow for completion.
Researcher-facing (score sheets and templates)	The ability of members of the research team, to complete OPTION(5) score sheets based on review of video-recorded consultations.	Inter-rater reliability of OPTION(5) scores will be evaluated by calculating the inter-class correlation coefficient on ratings of all videos, aiming for values above 0.75. Comparisons will be made with other studies. The completeness and usability of video-recordings will also be reviewed as described above.	Review of training procedures for OPTION(5) measure if correlation low. Review of appropriateness of the measure in the context of this study if training appears sufficient. Consideration of the need for development of an alternative measure to be piloted ahead of a definitive trial.

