**Clinical outcomes**					
Putative primary outcome					
Ratings of shared decision-making during the consultation from an observer perspective.	During data analysis	Assessment of video’d consultations by two trained researchers using the OPTION(5) score ([18] [19];)	18 GPs, 180 patients (9 GPs and 90 patients per arm)	Continuous (OPTION score 0-100%)	Mean and standard deviation, to report data descriptively. Linear hierarchical modelling to estimate between group differences* (random effect on cluster, adjustment for practice location).
Additional outcomes					
Patient-reported rating of involvement in decision-making about their healthcare	Immediately following the index consultation	Patient post-consultation questionnaire—using collaboRATE score ([18] [19];)	180 patients (90 per arm)	Continuous (collaboRATE score 0–100%)	Mean and standard deviation, to report data descriptively. Linear hierarchical modelling to estimate between group differences^a^ (random effect on cluster, adjustment for practice location). Patient and GP scores compared using logistic regression modelling (patient scores as outcome, GP scores as explanatory variable).
Patient-reported rating of feeling satisfied with the healthcare received	Immediately following the index consultation	Patient post-consultation questionnaire	180 patients (90 per arm)	Categorical, ordinal (3 point Likert scale)	Frequencies, to report data descriptively. Logistic hierarchical modelling to estimate between group differences^a^ (random effect on cluster, adjustment for practice location).
Patient-reported rating of having trust in the GP they saw				Categorical, ordinal (3 point Likert scale)	Frequencies, to report data descriptively. Logistic hierarchical modelling to estimate between group differences^a^ (random effect on cluster, adjustment for practice location).
Patient-reported rating of enablement				Discrete (PEI score 0–12)	Frequencies, to report data descriptively. Logistic hierarchical modelling to estimate between group differences^a^ (random effect on cluster, adjustment for practice location).

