Participant experiences of the intervention, participants experiences of the study	Following receipt of participant post-consultation questionnaires and consent forms	Interviews with the participants from practices assigned to the intervention	9 GPs, 15 patients	Audio-recordings for qualitative analysis	Both deductive and inductive approaches to thematic analysis

^a^Between group differences will be reported using the appropriate outcome metric with 95% confidence intervals; no p-values will be reported in this feasibility study

Using an ‘intention to treat’ approach, participants will be analysed according to their randomised allocation irrespective of intervention actually received. However, all participants will be considered adherent by definition of the protocol. There is no mechanism by which participants in the control group could receive the intervention.

An intra-cluster correlation coefficient (ICC) will be calculated within each arm (intervention and control) for academic purposes; however, this will not be used to calculate a sample size for the future definitive trial; an estimated ICC, calculated from a large relevant routine dataset, will instead be sought [40].

The appropriateness of the outcome measures for use in a future, definitive trial of the intervention will be evaluated. The consistency with which certain outcome measures (e.g. OPTION(5), CollaboRATE, and those items taken from the GPPS survey) perform with the study population, when compared with previous performance in existing literature, will be reviewed. Findings will also be considered in the context of the internal consistency of performance of these measures within the participant sample. Consideration will be given as to whether the outcome measures chosen are sensitive to the effects of the intervention in the context of older people with multimorbidity in primary care, or whether there is a need for development of new measures.

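### Blinded scoring of OPTION(5) is ruled out for both planned raters on resource grounds, and the inter-rater coefficient cannot reveal expectation bias that they share

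*Protocol article*

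**What the plan says.** Under Randomisation and blinding, the protocol article says: "Blinding of the research team to outcome assessment will not be possible due to resource availability". Resources are the only reason given.

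The putative primary outcome is described in Table 4 as "Assessment of video’d consultations by two trained researchers using the OPTION(5) score". Under Collecting outcome measure data: "Two researchers will independently score each clinical decision made out of 100, with higher scores indicating better shared decision-making". Table 3 identifies the raters when it lists what is to be reviewed: "The ability of members of the research team, to complete OPTION(5) score sheets based on review of video-recorded consultations". The reliability check in Table 3 is "calculating the inter-class correlation coefficient on ratings of all videos, aiming for values above 0.75".

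The scores feed an arm comparison. The footnote to Table 4 says: "Between group differences will be reported using the appropriate outcome metric with 95% confidence intervals; no p-values will be reported in this feasibility study". Evaluation of outcome measures adds that the trial will consider whether the chosen measures can pick up the intervention's effects in this population.

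For the later trial, the section on recruitment capability, consent and randomisation says: "Consideration will be given to blinding the research team for data analysis in the future trial".

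**The concern.** OPTION(5) is an observer's judgement, so a rater who knows the arm can, without meaning to, score trained GPs higher. The article expects that participants will know their arm, so the patient and GP collaboRATE ratings cannot readily be protected. OPTION(5) is the one shared decision-making measure for which masking could be attempted, because it is scored afterwards from recordings. The article gives this up for both raters and does not say why coded recordings could not be scored by at least one rater who is not told the allocation.

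Two outputs are at stake: the preliminary arm difference with its confidence interval, and the conclusion on whether OPTION(5) is sensitive enough to be the primary outcome of the definitive trial. The trial also loses the chance to learn whether masked rating of these videos is workable, which is a natural question for a study that lists potential outcome measures and data collection among its feasibility objectives.

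**Working it through.** The plan gives no figure for rater bias and no SD for OPTION(5), so there is nothing to reproduce. The check has a textual part and an illustrative part.

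**Are both raters covered by the no-blinding statement?** The statement concerns the research team. Table 3 calls the OPTION(5) raters members of that team. Neither Table 4 nor the data collection section exempts one of them. So both are covered. That they score knowing the arm is a direct inference from this; the article does not say that they are told it.

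**Does the stated reason settle the matter?** Two raters are already planned, they score independently, and agreement is computed on all videos. Scoring uses recordings, so it does not require a rater to visit a practice. Coding files and mixing their order are handling steps. Whether one rater can be kept unaware depends on who the raters are, which the article does not say.

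**Can the inter-rater coefficient detect a shared shift?** Let a single rater's score have within-arm variance 1, of which *r* is true between-video variance and 1 − *r* is rater error. Let both raters add a shift *b* (in within-arm SDs) to every intervention video. With 1:1 allocation the shift adds *b*²/4 to the variance that the raters share:

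ICC = (*r* + *b*²/4) / (1 + *b*²/4)

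With *r* = 0.75, the plan's target:

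- *b* = 0.25: (0.75 + 0.0156) / 1.0156 = 0.754
- *b* = 0.50: (0.75 + 0.0625) / 1.0625 = 0.765
- *b* = 0.75: (0.75 + 0.1406) / 1.1406 = 0.781

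With *r* = 0.60 the results are 0.606, 0.624 and 0.649. A shared shift raises the coefficient slightly and never lowers it.

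**Bias of the arm difference** (two-rater mean, no real effect assumed):

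| Shift *b* (SD, assumed) | Both raters unmasked: *b* | One fully masked, scores averaged: *b*/2 | Masked rater's score alone |
|---|---|---|---|
| 0.25 | 0.25 | 0.125 | 0 |
| 0.50 | 0.50 | 0.25 | 0 |
| 0.75 | 0.75 | 0.375 | 0 |

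On the score's own scale, assuming an SD of 15 points and a shift of 2 to 8 points, the displacement is 2/15 = 0.13 SD to 8/15 = 0.53 SD.

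**Are the arm-specific SDs affected?** Adding the same constant to every score in one arm leaves that arm's SD unchanged. Only a shift that varies between videos changes it. For example, an independent shift with an SD of 0.25 (assumed) gives √(1 + 0.25²) = √1.0625 = 1.03 times the original SD.

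**The case against.** The case on the other side has weight.

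- **The limitation is disclosed and the consequence is bounded.** This is a feasibility trial with no power calculation, hypothesis test or p-value, and participant response is its last, tentative objective. The only progression criterion on videos concerns how many are useable. This stands, and it limits the importance of the point.
- **Capacity is limited.** A reader might infer that one rater could be masked with no extra staff. The documents do not show this. The raters are not identified, neither is shown to be free of trial conduct, and Strengths and limitations of the study describes a doctoral fellowship with restricted resources and researcher time.
- **The video can reveal the arm.** Intervention patients are meant to voice a phrase from the tool, and trained GPs rehearse the VOLITION model. With about ten patients per GP, one revealing video can unmask that GP's others. Masking would be imperfect; how far it fails is itself worth measuring.
- **SD estimation is the purpose stated for the sample size.** A reader might infer that the arm-specific SDs are distorted. A constant shift does not do that.
- **Future blinding may already cover rating.** A reader might conclude that the later trial would mask only the analysis. Table 4 times the OPTION(5) rating within data analysis, so the sentence on the future trial may include it. It is unclear rather than wrong.
- **Other checks exist.** Comparison with other studies and internal consistency are also planned, so the coefficient does not stand alone. Neither of them tests expectation bias.
- **Using only a masked rater's score discards a second rating.** This costs reliability, so the two-rater score should be kept.

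File coding could be left to a full protocol. The statement that blinding is not possible is in the article itself, so it is open to comment.

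**Conclusion.** The point holds at modest weight. Blinded assessment of the putative primary outcome is given up for both raters with only a general appeal to resources, although two raters working from recordings are already planned. The planned inter-rater check cannot detect a shift that both raters share. An OPTION(5) difference in favour of the intervention, and any conclusion that the measure is sensitive to it, would therefore be open to rater expectation as an explanation.

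The size is unknown. The illustrations assume a constant shift shared by both raters, and for the points scale an SD of 15; none of these values comes from the documents. The no-test design and the progression criteria are untouched, and the arm-specific SDs are affected only if the shift varies between videos.

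**What to change.** Amend Randomisation and blinding in the protocol article as follows.

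1. Video files carry a study code showing neither practice nor arm, and are rated in random order mixed across arms.
2. Among the raters already planned, any rater not involved in the workshop or practice set-up is not told the allocation.
3. The planned two-rater score is kept, and the arm difference is also reported separately by rater.
4. Each masked rater records a guess of the arm after scoring each video.
5. In the recruitment capability, consent and randomisation section, state that the blinding considered for the future trial includes video rating.

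The cost is minor file handling and one extra item on the score sheet. Masking will be incomplete where patients voice tool phrases or GPs use the VOLITION model; the guesses and the by-rater comparison give an indication of how much this matters. If neither planned rater can be kept unaware of allocation, the protocol should say so and present the OPTION(5) difference as unmasked.
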